### Criteria for discontinuing or modifying interventions

Immunonutrition has been used for more than 15 years and no critical safety issues have been reported. Side effects (i.e., severe diarrhea or nausea requiring medical attention) related to the investigational product will not be considered as a criterion for discontinuation of the intervention.

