## Introduction

Radical cystectomy (RC) with extended bilateral pelvic lymph node dissection (PLND) represents the best available treatment for muscle-invasive BC [1]. Furthermore, this major surgery may be the treatment of choice for non-malignant pathologies, such as interstitial cystitis, painful bladder syndrome, neurogenic bladder, hemorrhagic radiation cystitis, infectious diseases of the bladder, endometriosis, and refractory genitourinary fistulae [2] in patients who have failed previous conservative therapy.

Although cystectomy is considered as an extended major surgery, it has unique features that preclude any outcomes extrapolation from other abdominal surgeries (i.e., colonic resections, gynecologic procedures). These include lymph node resection, longer operative time, significant bleeding, urinary diversion with bowel resulting in metabolic changes, and peritoneal soiling with urine [3].

Despite standardized surgical technique and the development of new perioperative care protocols, cystectomy morbidity remains a serious challenge for urologists. Postoperative complications lead to longer length of stay and worse survival. Infectious complications, including pneumonia, urinary tract infections, surgical site infections, septicemia, and shock, are relatively frequent after cystectomy, rated between 25 and 45% [4, 5]. Patients undergoing cystectomy for a bladder cancer or a benign disease have the similar risk of complications [6]. Antibiotic prophylaxis practices are highly heterogeneous in cystectomy and there is a lack of adherence in guidelines [7].

Careful perioperative risk reduction in patients undergoing major surgery is an evolving key concept to decrease postoperative morbidity rates. Many risk factors, such as repeated radio-chemotherapy regimens, pre-existing co-morbidities, and increased age, can hardly be influenced. Although malnutrition has been identified as an independent risk factor for morbidity and mortality after cystectomy [8–10], there is no recommendation with regard to preoperative screening and/or treatment of malnutrition in guidelines for cystectomy. In most of hospitals where cystectomies are performed, there is no standardized malnutrition screening policy and malnourished patients undergoing surgery are therefore neither identified nor treated.

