**Fig. 1 Fig1:**
[figure not shown]
Inclusion and exclusion criteria of the INCyst Trial

**Table 1 Tab1:** Trial registration data set according to World Health Organization

Data category	Information
Primary registry and trial identifying number	ClinicalTrials.gov NCT05726786
Date of registration in primary registry	March 9, 2023
Secondary identifying numbers	2022–01528 (Swissethics); SNCTP000005406 (KOFAM)
Source(s) of monetary or material support	Swiss National Science Foundation
Primary sponsor	University Hospital of Lausanne (CHUV)
Secondary sponsor(s)	None
Contact for public queries	[name]. [name] ([contact])
Contact for scientific queries	[name]. [name] ([contact])
Public title	The impact of immunonutrition on postoperative complications in patients undergoing bladder removal surgery
Scientific title	The role of preoperative immunonutrition on morbidity and immune response after cystectomy: protocol of a multicenter randomized controlled trial (INCyst Trial)
Countries of recruitment	Switzerland
Health condition(s) or problem(s) studied	Determination of infectious complications rate at 30 days after surgery
Intervention(s)	Drug: Oral Impact^®^, Nestlé Health Science, Switzerland
Key inclusion and exclusion criteria	Inclusion criteria: age ≥ 18 years, patient undergoing open cystectomy (for all reasons) Exclusion criteria: contraindications to immunonutrition (e.g., known hypersensitivity or allergy to lactose, fish oil, or soy lecithin), severe diarrhea requiring medical attention, current treatment with any immunosuppressive drug
Study type	Multicenter, prospective, controlled, pragmatic, parallel-group comparative study with block randomization stratified by centers
Date of first enrolment	April 2023
Target sample size	232
Recruitment status	Recruiting
Primary outcome(s)	Determination of the Comprehensive Complication Index (CCI) at 30 and 90 days after surgery Determination of the mortality rate at 30 and 90 days after surgery Determination of the postoperative complication-free survival
Key secondary outcome	Identification of biomarkers predictive of postoperative complications studying the patient’s immune and microbiome signature

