### Follow-up of adverse events (AE)

No AE related to the intake of immunonutrition are expected and therefore only 30-day and 90-day postoperative surgical complications will be reported to evaluate primary and secondary endpoints. All serious AEs will be followed until they are resolved or stabilized, including after the end of the study. If immediate safety and protective measures have to be taken during the conduct of the study, the investigator notifies the local ethics committee of these measures, and of the circumstances necessitating them, within 7 days.

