### Choice of comparators and protocol adherence

Oral Impact^®^ (IN) is an immune-modulating nutritional supplement containing arginine, omega-3 polyunsaturated fatty acids, and ribonucleic acid. Arginine is a key amino acid involved in multiple cellular processes as well as in lymphocyte function and its deficiency results in impaired adaptive immune response. It plays an active role in wound healing, muscle repair (by protein translation), and thrombosis prevention. The present design raises the issue of supplementing patients that are not at nutritional risk with Oral Impact®, resulting in overnutrition with potentially deleterious clinical consequences. However, this hypothesis has not been confirmed by others [23] and the product’s brochure stipulates that the administration of Oral Impact® in the preoperative phase is also indicated in well-nourished patients [24]. Moreover, surgery induces arginine deficiency and many patients with normal preoperative arginine concentrations cannot endogenously satisfy the metabolic demand after surgery.

Patients will be randomly assigned to receive 7 days of preoperative IN, three times a day (Oral Impact^®^) or will not receive oral IN supplements. Carbohydrate loading and protein drinks will be allowed in both groups. In the interventional group, patient’s compliance to the allocated treatment will be recorded by asking the patient how many nutritional supplements she/he has ingested preoperatively (ranging from 0 to 21 bags). Compliant patients will be defined by having drunk at least 14 of the 21 allocated nutritional supplements. To objectively verify and validate these subjective data, serum arginine levels will be assessed at enrolment (between day − 30 and day − 8) and at preoperative admission after intake of the allocated nutrition (day − 1).

Potential effective crossover between intervention groups will be assessed and recorded. As usual with interventions requiring voluntary adherence to a protocol, there is a risk for some participants from the IN arm do not comply with the intervention. Moreover, a mirroring risk exists for participants from the control group to access IN independently of the study protocol, since the product is commercially available. Recording such protocol deviations is mandatory for processing to a second line per-protocol analysis. However, the risks of crossover are very low.

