### Statistical analysis

Ordinal and continuous data will be presented by study group in the form of descriptive statistics, as number of patients, mean, standard deviation, minimum, median, and maximum. Categorical data will be presented by study group using contingency tables with absolute and relative frequencies.

Complications rate will be presented using contingency tables with absolute and relative frequencies, overall and then by study group. The complication rate will be compared between groups using a Chi2 test. Mortality after surgery and postoperative complication-free survival will be analyzed using Kaplan–Meier curves. The study groups will be compared with a log-rank test. Nutritional status will be documented, and subgroup analysis of well-nourished patients randomized to the IN group will be undertaken at the end of the study. No imputations will be done on missing data. So, for longitudinal analysis mixed method analysis will be performed. Non-compliant patients from both arms will be maintained in the study, with no exclusion from the primary intention-to-treat analysis, however withdrawn from the per-protocol analysis. There is no data monitoring committee, owing to very good and well-known safety profiles of the IN and to the short follow-up period.

Other subgroup analyses will be performed (1) to test the effect of neoadjuvant chemotherapy and the risk of malnutrition on the primary outcomes and (2) to test the impact of the ERAS® compliance on the primary and secondary outcomes.

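### The protocol rules out severe product-related diarrhea or nausea as a criterion for stopping the supplement before surgery, and the analysis does not need that rule

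*Protocol article*

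**What the plan says.** The section Criteria for discontinuing or modifying interventions has two sentences. The first refers to the product's long safety record. The second names the events, "Side effects (i.e., severe diarrhea or nausea requiring medical attention", and says that such events "related to the investigational product will not be considered as a criterion for discontinuation of the intervention". It gives no other criterion for stopping or reducing the supplement.

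Other sections that bear on the point:

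- **Follow-up of adverse events (AE):** no adverse events from the product are expected, and "only 30-day and 90-day postoperative surgical complications will be reported to evaluate primary and secondary endpoints". Serious events are followed to resolution. Immediate safety measures are to be notified to the ethics committee within 7 days.
- **Protocol amendments:** in an emergency, deviations that protect participants may go ahead without prior approval.
- **Choice of comparators and protocol adherence:** the regimen is three bags a day for 7 days. Non-adherence is foreseen ("As usual with interventions requiring voluntary adherence to a protocol"), intake is counted from 0 to 21 bags, and "Compliant patients will be defined by having drunk at least 14 of the 21 allocated nutritional supplements".
- **Statistical analysis:** "Non-compliant patients from both arms will be maintained in the study, with no exclusion from the primary intention-to-treat analysis". Such patients leave only the per-protocol analysis. There is no data monitoring committee.

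**The concern.** The sentence already grants that the event is severe, needs medical attention and is attributed to the product. In the week before open cystectomy, that is the situation in which an investigator would most want a written basis for stopping. The section that should supply one says instead that the event does not count. An investigator who stops the supplement for this reason acts without a protocol criterion and against the only one discussed. With no data monitoring committee, more rests on the written rule and the investigator's judgment.

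A rule of this kind is sometimes written to stop patients from being lost to the analysis. If that was the aim, the sentence addresses the wrong thing. It concerns discontinuation of the intervention, whereas retention in the study and in the analysis set is settled elsewhere. What is at stake is patient safety and clear conduct, not the validity of the primary comparison.

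**Working it through.** **1. Does any section supply a stopping criterion?**

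| Section of the protocol article | What it allows | Criterion for stopping the supplement? |
|---|---|---|
| Criteria for discontinuing or modifying interventions | Excludes severe product-related diarrhea or nausea as a criterion | No; it points against one |
| Follow-up of adverse events (AE) | Immediate safety measures, with notification | No; general route |
| Protocol amendments | Emergency deviations without prior approval | No; emergencies only |
| Choice of comparators and protocol adherence | Patient may take fewer bags; intake is recorded | No; the patient's choice |

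Three routes leave room to stop. None names a criterion.

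**2. Is the rule needed to keep patients in the analysis?** No. A patient who stops is non-compliant at most, and the Statistical analysis section keeps non-compliant patients in the intention-to-treat set. The number analysed is the same with or without the rule.

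**3. Effect on the per-protocol set.** The regimen is 3 bags × 7 days = 21 bags. The threshold is 14, so 21 − 14 = 7 bags (33%) may be missed. Four full days give 12 bags. The first bag of day 5 makes 13 (non-compliant) and the second makes 14 (compliant). Only a stop before the second bag of day 5 removes a patient from the per-protocol set.

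**4. Effect on power.** Inputs from Sample size calculations: p₁ = 0.37 (control), p₂ = 0.20 (IN), two-sided α = 0.05, power 80%, 110 per arm, dropout 5%.

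The plan's own figure first, with pooled variance under the null, no continuity correction and p̄ = (0.37 + 0.20)/2 = 0.285:

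- n = [1.960·√(2·0.285·0.715) + 0.842·√(0.37·0.63 + 0.20·0.80)]² / 0.17²
- = [1.960·0.638 + 0.842·0.627]² / 0.0289 ≈ 109.5, so **110 per arm**
- 220 / 0.95 = 231.6, so **232 enrolled**

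Both stated figures reproduce. Power at n per arm is

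Φ{ [(p₁ − p₂)·√n − 1.960·√(2p̄(1 − p̄))] / √(p₁(1 − p₁) + p₂(1 − p₂)) }.

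With n = 110 this is Φ[(1.783 − 1.251)/0.627] = Φ(0.848) = 80.2%.

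Now let a share s of the IN arm stop and revert fully to the control rate, so that p₂ = 0.20(1 − s) + 0.37s. The article gives no value for s, so the shares are assumptions:

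| s (assumed) | IN rate | Power at 110 per arm |
|---|---|---|
| 0% | 20.00% | 80.2% |
| 2% | 20.34% | 78.4% |
| 5% | 20.85% | 75.6% |
| 10% | 21.70% | 70.5% |

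For each s this is the worst case. It assumes that partial intake has no effect and that every stop is caused by the changed sentence. Affected patients who would have stopped anyway add nothing to the loss.

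**The case against.** The strongest defence is that the sentence may mean only that these events do not force withdrawal. Intake is voluntary, safety measures and emergency deviations are provided for, and the trial runs under Good Clinical Practice. On that reading an investigator can already stop the supplement, and a permissive replacement changes little. Much of this stands. It shows that the sentence does not order continued dosing, and it lowers confidence that any patient would be harmed. It does not turn the sentence into a stopping criterion, and the wording concerns the intervention, not study participation. If the milder meaning was intended, the replacement states it.

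A second defence is that a condensed article may leave stopping rules to the full protocol. That would excuse silence. It does not excuse an explicit rule.

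A third is that stopping dilutes the effect. That is correct, and the working shows by how much. Intention-to-treat fixes who is analysed and does not protect power. But a modest loss of power is no reason to discourage stopping in a patient with severe product-related symptoms.

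Two stronger readings are tempting:

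- A reader might infer a contradiction with the entry criteria in Table 1, which exclude "severe diarrhea requiring medical attention, current treatment with any immunosuppressive drug". The documents do not support that. The entry criterion concerns diarrhea present at enrolment, while the rule concerns later effects of the product. Nausea is not among the exclusions listed there. Entry and stopping criteria need not match.
- A reader might draw support from the Introduction, which lists "urinary diversion with bowel resulting in metabolic changes" among the features of cystectomy. That passage explains why results from other abdominal operations do not carry over. It says nothing about diarrhea or nausea before surgery.

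**Conclusion.** The point holds as a minor matter of safety and conduct, with moderate confidence. The protocol article explicitly rules out severe product-related diarrhea or nausea as a criterion for stopping the supplement, and no other section supplies a criterion. The rule does nothing for the analysis set, which the intention-to-treat provision already protects.

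The rule covers the 116 patients of the IN arm over 7 days. No count of affected patients can be given, because the article reports no incidence. The stated sample size is correct and need not change. A reader might infer that the change is free of statistical cost. It is not quite: under the assumed stopping shares of 2% to 10%, power would be at worst 78.4% to 70.5% instead of 80.2%. The true loss is smaller to the extent that affected patients would have stopped anyway or that partial intake keeps some effect.

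**What to change.** Replace the second sentence of Criteria for discontinuing or modifying interventions with:

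> *The supplement may be interrupted or stopped for product-related severe diarrhea or nausea requiring medical attention; the patient remains in follow-up and in the intention-to-treat analysis, and the reason for stopping is recorded with the bag count.*

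This permits stopping without requiring it and separates stopping the product from leaving the study. It also adds tolerability data to a bag count that is already collected.

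The cost is one sentence in a protocol amendment, possibly a few more patients below 14 bags and so outside the per-protocol set, and the limited dilution described above. The planned enrolment and the primary analysis stay as they are.

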### Monitoring

The monitoring will be performed by the clinical trial unit of Lausanne, in accordance with ICH GCP E6(R2). The monitor (independent of the research team) will carry out this activity according to a pre-established monitoring plan adapted to the risk of the clinical trial. The monitor will verify that the clinical trial is conducted, and that the data are generated, documented, and reported in accordance with the requirements of the protocol, the GCP, and the applicable regulatory requirements. In concrete terms, an initiation visit, intermediate visits, and a closing visit will be organized on each site by the monitor in accordance with the monitoring plan. At each site, the local principal investigator will ensure that the monitor always has access to the trial data and source documents and will respond to questions and requests for corrections during the monitoring visits.

### Choice of comparators and protocol adherence

Oral Impact^®^ (IN) is an immune-modulating nutritional supplement containing arginine, omega-3 polyunsaturated fatty acids, and ribonucleic acid. Arginine is a key amino acid involved in multiple cellular processes as well as in lymphocyte function and its deficiency results in impaired adaptive immune response. It plays an active role in wound healing, muscle repair (by protein translation), and thrombosis prevention. The present design raises the issue of supplementing patients that are not at nutritional risk with Oral Impact®, resulting in overnutrition with potentially deleterious clinical consequences. However, this hypothesis has not been confirmed by others [23] and the product’s brochure stipulates that the administration of Oral Impact® in the preoperative phase is also indicated in well-nourished patients [24]. Moreover, surgery induces arginine deficiency and many patients with normal preoperative arginine concentrations cannot endogenously satisfy the metabolic demand after surgery.

Patients will be randomly assigned to receive 7 days of preoperative IN, three times a day (Oral Impact^®^) or will not receive oral IN supplements. Carbohydrate loading and protein drinks will be allowed in both groups. In the interventional group, patient’s compliance to the allocated treatment will be recorded by asking the patient how many nutritional supplements she/he has ingested preoperatively (ranging from 0 to 21 bags). Compliant patients will be defined by having drunk at least 14 of the 21 allocated nutritional supplements. To objectively verify and validate these subjective data, serum arginine levels will be assessed at enrolment (between day − 30 and day − 8) and at preoperative admission after intake of the allocated nutrition (day − 1).

Potential effective crossover between intervention groups will be assessed and recorded. As usual with interventions requiring voluntary adherence to a protocol, there is a risk for some participants from the IN arm do not comply with the intervention. Moreover, a mirroring risk exists for participants from the control group to access IN independently of the study protocol, since the product is commercially available. Recording such protocol deviations is mandatory for processing to a second line per-protocol analysis. However, the risks of crossover are very low.

### Protocol amendments

Substantial changes to the study setup and study organization, the protocol, and relevant study documents will be submitted to the local ethics committee for approval before implementation. Under emergency circumstances, deviations from the protocol to protect the rights, safety, and well-being of human subjects may proceed without prior approval of the local ethics committee. Such deviations shall be documented and reported to the ethics committee as soon as possible.

### Roles and responsibilities

The sponsor is the University Hospital of Lausanne (CHUV), which is responsible for providing to the investigator the necessary information to conduct the clinical trial, to ensure proper monitoring of the trial and certifying compliance to ethical bodies and Swiss legislation. The sponsor can be contacted by email ([contact]). The coordinating center is the Department of Urology of CHUV.

A dedicated research nurse, urologist, and data manager in each participating center are responsible for all aspects of local organization, including identifying potential recruits and taking informed consent. A dedicated urologist from the coordinating center (Department of Urology of the CHUV) will be responsible for the grading of postoperative complications. The assessor will be blinded but not the data analyst. The Urology Research Unit will be responsible for the translational research (exploratory outcomes).

### Data management system

The study coordinator will be responsible for entering relevant data from the eCRF or results from the laboratory in Excel data bases. Data generation, transmission, archiving, and analysis of personal data within this study will strictly follow the applicable Swiss legal requirements for data protection. Study data will be entered into the eCRF. The REDCap^®^ software will be used and is validated by the Lausanne University Hospital for the research data management. Prerequisite is the voluntary approval of the subject given by signing the informed consent prior to start of participation in the clinical trial. REDCAP^®^ database runs on a server maintained by the IT Department of the Lausanne University Hospital.

